# Intertruncal versus classical approach to the ultrasound-guided supraclavicular brachial plexus block for upper extremity surgery: study protocol for a randomized non-inferiority trial

**DOI:** 10.1186/s13063-022-06029-x

**Published:** 2022-01-29

**Keywords:** Intertruncal approach, Ultrasound, Brachial plexus block, Supraclavicular, Double-injection technique

## Abstract

**Background:**

Ultrasound-guided intertruncal approach (IA) to the supraclavicular block (SB) is recently proposed as a new approach for local anesthetic (LA) injection in terms of the classical approach (CA) at the level of the first rib. The CA-SB has been proven to result in satisfying sensorimotor block, but associate with a high risk of intraneural injection. The aim of this randomized non-inferiority study is to explore whether IA-SB can obtain similar block dynamics, as the CA-SB, but avoiding an intraneural injection during the whole nerve block procedure.

**Methods:**

The total 122 patients undergoing elective upper extremity surgery will be randomly allocated to receive either an IA-SB or a CA-SB using a double-injection (DI) technique. In the IA-SB group, a portion of LA (15 mL) is injected accurately to the intertruncal plane between the middle and lower trunks under real-time ultrasound guidance; then, the remaining volume (10 mL) is carefully distributed to the other intertruncal plane between the upper and middle trunks. In the CA-SB group, the DI technique will be carried out as described in Tran’s study. The primary outcome is the percentage of patients with a complete sensory blockade at 20 min with a predefined non-inferiority margin of − 5%. The secondary outcomes include the sensory-motor blockade of all 4 terminal nerves, onset times of the individual nerves within 30 min, block-related variables, and adverse events.

**Discussion:**

The results will provide sensory-motor blockade-related parameters and safety of the ultrasound-guided intertruncal approach to the supraclavicular block, thereby promoting clinical practice.

**Trial registration:**

Chinese Clinical Trial Registry ChiCTR2000040199. Registered on 25 November 2020

**Supplementary Information:**

The online version contains supplementary material available at 10.1186/s13063-022-06029-x.

## Background

The supraclavicular block (SB) is a popular and approved approach to the brachial plexus because of the greater safety due to real-time ultrasound guidance and better block dynamics known as the “spinal anesthesia of the arm” [1, 2]. Compared with its single- or multiple-injection counterpart, a double-injection (DI) technique has been widely used in the classical approach (CA), which is at the level of the trunks and divisions [3–11]. However, all these techniques are associated with a high risk of intraneural injection, which is known as the sub-epineurium or intracluster injection. Recently, Siddiqui et al. [12] have proposed an alternative approach using the DI technique based on the clear identification of the outer boundaries (epineurium) of each trunk (upper, middle, and lower), named the intertruncal approach (IA). The double injection in IA aims to provide satisfying block dynamics of the entire brachial plexus while avoiding intraneural injection, by which local anesthetic (LA) is accurately deposited to adipose tissue planes between the upper and middle, and the middle and lower trunks. Although the DI techniques (CA vs IA) require injection of LA very close to contiguous compartments of the brachial plexus, there are essential differences between the two approaches with respect to the injected location of LA [2, 13]. In addition, different approaches direct toward the same goal for better block dynamics, that is, LA spreads evenly within the entire brachial plexus sheath without any nerve sparing [11].

Given that, the DI technique has been associated with less needle passes and results in satisfying block dynamics for ultrasound-guided CA-SB [7]. However, no clinical study data about block dynamics, including the proportion of patients with complete sensory-motor blockade and onset times, are available for IA-SB until now. Therefore, our hypothesis in this study is that the novel IA-SB will obtain comparable block dynamics when compared with CA-SB; meanwhile, it is a promising method of placing the LA immediately adjacent to the trunks without the risk of intraneural injection.

## Methods/design

### Trial design and setting

This prospective, non-inferiority, parallel randomized controlled trial will be carried out at the Third Affiliated Hospital of Sun Yat-sen University, China. It is developed according to the Recommendations for Interventional Trials (SPIRIT) 2013 Statements that came from the Standard Protocol Items (Fig. 1, the SPIRIT Checklist is available as Additional file 1) [14]. Besides, the Consolidated Standards of Reporting Trials (CONSORT) flow diagram will be performed in the design period and completing the study to the end. A detailed flowchart of the trial design is shown in Fig. 2.

**Fig. 1 Fig1:**
[figure not shown]
The standard protocol items of this study

**Fig. 2 Fig2:**
[figure not shown]
Flow diagram of this study

### Informed consent

Written informed consent will be obtained from each patient before enrollment. The ultrasound-guided IA- or CA-SB-related operation sequence, benefits, risks, and data privacy of this study will be explained in detail for the participants during the preoperative visit. We will emphasize that this study is voluntary, and the participants are free to withdraw from the study at any time. If the patient is not willing to participate in the study, he or she will receive other means of brachial plexus block or general anesthesia depending on the patient’s willingness and discretion of the treating anesthesiologist.

### Participants and recruitment

The patients scheduled to undergo surgery of the elbow, forearm, wrist, or hand with ultrasound-guided brachial plexus block will be recruited and screened for eligibility in our medical center. An independent researcher will conduct the recruitment when performing the preoperative visit 1 day before surgery.

Inclusion criteria are as follows:
Signed written informed consentAmerican Society of Anesthesiologists (ASA) physical status I to IIIAge 18 to 75 years oldOperative site at the elbow, forearm, wrist, or hand

Exclusion criteria are as follows:
Patient’s refusal of brachial plexus blockNerve block cannot be performed due to coagulopathy (defined as any coagulation disorders contraindicated to perform peripheral nerve block), pre-existing neuropathy, infection at the supraclavicular fossa, hypersensitivity, or allergy to LABody mass index (BMI) > 35 kg/m^2^Pregnancy, severe mental illness, or cognitive dysfunction (unable to communicate or cooperate)

### Randomization and blinding

After the enrollment, the participants were randomly allocated to one of the two groups (CA-SB or IA-SB group) in a 1:1 ratio by computer-generated simple randomization. A sealed opaque envelope that contained a card (recorded with a random number and subject number) will be opened by a research assistant who will not be involved in other stages of this study. Ultrasound-guided CA-SB or IA-SB will be carried out by one out of our nerve block team ([name], [name], and [name]) and supervised by the coauthor ([name]), in which all have extensive experience with both techniques (over 60 attempts/per technique) before this study. Another anesthesiologist who is blinded to the randomized allocation and intervention will be responsible for recording the research-related variables and anesthesia management based on the conventional scheme. During the study period, research assistants who will be kept blind to the group allocation oversaw postoperative follow-up by face-to-face assessment or telephone. If a serious adverse event (pneumothorax or LA systemic toxicity, etc.) occurs during the nerve block, un-blinding will be permissible, and then emergency measure will be initiated under the supervision of the outcome assessor.

### Ultrasound-guided techniques

All participants will be seen on 1 day before surgery and demonstrated on the use of a 3-point scale for evaluating sensory-motor blockade. On arrival to the operating room, standard ASA monitors (non-invasive cuff blood pressure, pulse oxygen saturation, and electrocardiogram) and supplemental oxygen (nasal cannula at 4 L/min) will be applied. An intravenous access (20-gauge) for fluid infusion will be established in the contralateral forearm, and the premedication (midazolam 0.05 mg/kg or combined with fentanyl 0.5 μg/kg) will be given prior to nerve block. Drugs that improve the block effect or duration of the sensory-motor blockade will be not allowed to use in the perioperative period, including dexmedetomidine or dexamethasone or magnesium sulfate. All patients will be received EtCO_2_ in monitoring during procedure and surgery. For the two approaches, the nerve block will be performed following standard skin disinfection with a portable ultrasound machine (Sonosite M-turbo, SonoSite, Inc., Bothell, WA) and 80-mm short-beveled stimulating needle (B. Braun Melsungen AG, Melsungen, Germany).

The ultrasound-guided CA-SB with the DI technique will be performed in accordance with the method described in Tran’s study [3]. After obtaining a satisfactory image of elliptical hypoechoic trunks and divisions at the supraclavicular fossa, the operators initially orientate the needle tip to the “corner pocket” between the subclavian artery and the lower trunk with the in-plane technique. A part of the LA (15 mL) of 1:1 mixture of 2% lidocaine (Shandong Hualu Pharmaceutical Co., Ltd.) and 1% ropivacaine (Astrazeneca Pharmaceutical Co., Ltd.) will be injected after the accurate position is confirmed by the “water separation” technique under ultrasound guidance. Subsequently, the needle will withdraw and targets the center of the main neural cluster floated upward by the former LA. The remaining volume (10 mL) will be carefully administered into that central position.

For the ultrasound-guided IA-SB, the procedures with the DI technique are replicated from Siddiqui’s study [12] and the optimal order of injections will be followed according to the suggestion in Endersby’s letter [15]. Using a high-frequency pattern, a consecutive scan will be performed initially at the supraclavicular fossa toward the base of the neck in a coronal oblique plane. Once the three trunks of the plexus (upper, middle, and lower) and its epineurium are well defined, the needle is advanced from the lateral end of the probe, and the first part of LA (15 mL) will be accurately injected into the intertruncal plane between the middle and lower trunks. It is worth noting that each trunk is in a different stage of its trajectory and those divisions have not been fused with each other yet in this area. Then, the second placement of LA (10 mL) is carefully distributed to the other intertruncal plane between the upper and middle trunks.

### Outcome definitions and evaluations

The definitions and evaluations of the primary and secondary outcomes of this study are summarized in Table 1.

**Table 1 Tab1:** Outcome definitions and evaluations

	Definition	Evaluation
**Primary outcome**		
The percentages of patients with a complete sensory blockade at 20 min	The combined score is equal to or greater than 7 points.	The sensory blockade of the 4 terminal branches of the brachial plexus is evaluated and graded every 5 min until 30 min after injection using a validated 3-point scale*.
**Most important secondary outcomes**		
Nerve injury	The percentages of patients who have been associated with persistent paresthesia or weak of the operative upper limb.	7 days after surgery via post-operation follow-up at the ward or telephone follow-up.
Incidence of adverse events	The percentages of patients who have been occurred with vascular puncture, Horner syndrome, toxicity of LA, or pneumothorax.	According to drawing with blood, real-time ultrasonic image, and (or) the patient’s symptoms. A detailed description is seen in the footnote^£^.
Diaphragmatic paralysis	The excursion of the ipsilateral hemidiaphragm will be measured by ultrasound in supine position via the anterior subcostal route in centimeters.	Using ultrasonic evaluation at 35 min after injection.
**Other secondary outcomes**		
Imaging time	Defined as the time from initial contact of the ultrasound probe with the skin until obtaining satisfactory imaging.	A stopwatch to calculate
Needle time	Defined as the time from initial needle insertion until the complete injection of the LA.	A stopwatch to calculate
Performance time	Defined as the imaging time plus the needle time.	/
Satisfactory imaging	Defined as more than 4 divisions of the plexus should be visualized as hypoechoic circular structures lateral to the subclavian artery for the CA-SB, and all 3 trunks of the plexus (upper, middle, and lower) for IA-SB.	Real-time ultrasonic image
Needle pass	Defined as at least 10-mm withdrawal of the needle to retract its trajectory.	During puncture
Needle visual score	Converted into a 5-point scale^§^	Assessment will be made at the time when the first proper position for LA injection is confirmed.
Procedural-related pain	Converted into the numeric rating scale (NRS)	NRS: 0 = no pain, 10 = worst possible pain
Difficult level	Converted into the NRS	NRS: 0 = no difficulty, 10 = extremely difficulty
Surgical anesthesia	Defined as one can tolerate surgical stimulus	During skin incision
The percentages of patients with a complete sensory or motor blockade	The combined score is equal to or greater than 7 points.	The percentages of patients with complete sensory or motor blockade using a validated 3-point scale^#^ every 5 min until 30 min after injection.
Sensory onset time	The time point when combined score is equal to or greater than 7 points.	Using a validated 3-point scale every 5 min until 30 min after injection.
Motor onset time	The time point when combined score is equal to or greater than 7 points.	Using a validated 3-point scale every 5 min until 30 min after injection.
Sensory-motor onset time	The time point when the combined score is equal to or greater than 14 points.	Using a validated 3-point scale for complete sensory-motor blockade every 5 min until 30 min after injection.
Duration of the sensory-motor blockade	Converted into the NRS	0 = normal compare that to the contralateral upper limb, 10 = no feeling or complete in-mobility; sensory-motor blockade return to normal will be defined as NRS<3.

*3-point scale for sensory blockade: 0 = no block, 1 = partial anesthesia, 2 = complete anesthesia

^£^Vascular puncture is defined as the needle is placed at the optimal location and withdraws with blood before injection under ultrasound guidance. Horner syndrome consisted of the occurrence of symptoms of miosis, ptosis, and hyperemia observed by anesthesiologists within 30 min after injection. Toxicity of LA consisted of the occurrence of signs of agitated, paresthesia, tinnitus, vertigo and perioral numbness, and convulsions, etc., due to central nervous system toxicity observed by anesthesiologists within 30 min after injection. Pneumothorax will be assessed by chest X-ray when the needle accidentally punctures the pleura during performing the block, or the patient feels ipsilateral chest pain, and/or is accompanied by symptoms of severe chest tightness or dyspnea

^§^5-point scale for needle visual score: 1 = very poor, 2 = poor, 3 = fair, 4 = good, and 5 = very good

^#^3-point scale for motor blockade: 0 = no block, 1 = paresis, and 2 = paralysis

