### Sample size calculation and statistical analysis

Our working hypothesis is that ultrasound-guided CA- versus IA-SB yield similar block dynamics. Thus, this study will be designed as a non-inferiority trial. In the previous studies using single or multiple injections in SB, we have observed that the proportion of patients with complete sensory blockade reached a plateau starting at 20 min after injection. It fluctuates between 70% and close to 100% within 30 min [3–6, 16]. In other words, relative to itself, the variation is very subtle from 20 to 30 min. The primary outcome is considered as the proportion of patients with complete sensory blockade of all 4 terminal nerves at 20 min after injection in this study. Based on a pilot study with 15 patients in each group, the proportion of patients with complete sensory blockade achieved was 73% in the CA-SB group and 87% in the IA-SB group (unpublished data). Therefore, we assume that a difference in proportion between the two groups less than − 5%, measured at 20 min after injection, will be considered non-inferiority. The required sample size per group is calculated to be 55 with a statistical power of 80% and a one-sided 95% confidence interval. To account for a possible 10% dropout rate, the total sample size is inflated to 122 participants (*n* = 61, per group).

Statistical analysis will be performed using *SPSS for Windows 18.0* (SPSS Inc., Chicago, IL). For continuous data, normality will be first assessed with the *Kolmogorov-Smirnov test* and then analyzed using an *independent-samples t test.* Categorical variables will be summarized as a frequency, *n* (%), such as the proportion of complete sensory or motor blockade, success rates, and adverse events, etc. The *Pearson χ*^*2*^
*test*, *Fisher’s exact test*, or a *Mann-Whitney U test* will be used for categorical variables as appropriate. A *p < 0.05* will be considered statistically significant for all results.

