The development of a new-style approach or needling technique is coming into clinical practice because the advancement in ultrasound guidance allowed for a further understanding of the underlying anatomy of the brachial plexus (trajectory and surrounding fascial sheath) [23]. For instance, the selective trunk block which is a novel brachial plexus block technique is just inspired by accurately identifying the main components of the plexus above the clavicle under real-time visualization and is expected to result in producing surgical anesthesia of the whole upper extremity [24, 25]. Recently, Siddiqui and colleagues [12] have proposed an alternative approach to the classical approach to a SB, in which LA is carefully injected into the investing adipose layers between the trunks. This is a very promising needling technique without intraneural injection for ultrasound-guided SB. However, the specific data of block dynamics is not yet clear compared with the classical approach. The objective of this study was to assess the block dynamics and clinical feasibility with DI in the supraclavicular fossa via IA.

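### Sensory and motor blockade are compared at each time only after a cut at 7 of 8 points; adding a comparison of the full scores would recover some power at little cost

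*Protocol article*

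**What the plan says.** The primary outcome row of Table 1 fixes the schedule: "The sensory blockade of the 4 terminal branches of the brachial plexus is evaluated and graded every 5 min until 30 min after injection". The footnotes give the grades: "3-point scale for sensory blockade: 0 = no block, 1 = partial anesthesia, 2 = complete anesthesia" and "3-point scale for motor blockade: 0 = no block, 1 = paresis, and 2 = paralysis".

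Under the other secondary outcomes in Table 1, the repeated comparison is "The percentages of patients with a complete sensory or motor blockade", defined by "The combined score is equal to or greater than 7 points". Sensory and motor onset are each "The time point when combined score is equal to or greater than 7 points", and sensory-motor onset uses 14 or more on the two scores together.

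The section on sample size and statistical analysis summarises categorical variables as n (%), "such as the proportion of complete sensory or motor blockade, success rates, and adverse events, etc". It names Pearson, Fisher and Mann-Whitney tests for categorical variables and a t test for continuous data, but ties none of them to a 0 to 8 score. The Discussion gives the aim: "The objective of this study was to assess the block dynamics and clinical feasibility with DI in the supraclavicular fossa via IA".

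**The concern.** Every Table 1 blockade outcome built on the combined score passes through the same cut. At each assessment, scores 0 to 6 count as one value, and 7 and 8 count as another. At 5 and 10 minutes few patients are likely to have reached 7, so a difference in how fast the block builds up shows mainly in scores that the comparison does not separate. Around 20 minutes the reverse holds: many patients are at 7 or 8, and the cut does not separate those two.

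The result is up to twelve yes/no comparisons (two modalities at six times), each less sensitive than the recorded data allow. The working hypothesis is that the two approaches behave similarly. An insensitive comparison that finds no difference could then be read as support for it.

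**Working it through.** **The plan's own figure.** The inputs are 73% and 87% complete sensory block in the pilot, a margin of −5 points, one-sided 5% and 80% power. With n = (1.645 + 0.842)² × V / (0.14 + 0.05)² and (1.645 + 0.842)² = 6.183:

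- unpooled, V = 0.73×0.27 + 0.87×0.13 = 0.3102, n = 53.1, so 54;
- pooled, V = 2×0.80×0.20 = 0.32, n = 54.8, so 55.

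The stated 55 per group reproduces, and 55 × 1.1 = 60.5 gives 61. The document states no power for the secondary comparisons.

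**Power with and without the cut at one time.** Assumptions: 55 per arm, two-sided 5%, and one common odds ratio at every cut, taken from the pilot: (0.87/0.13)/(0.73/0.27) = 2.475, ln = 0.906, squared 0.821. The document gives no score distributions, so several are tried. For an ordinal score under proportional odds, power is approximately Φ(z − 1.96), with

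z = √[2n × (ln OR)² × (1 − Σp̄³) / 12],

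where p̄ is the share of patients in each score category, averaged over the arms.

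- Cut at 7, 20 minutes: p̄ = 0.20 and 0.80, 1 − Σp̄³ = 0.480, z = 1.90, power 48%. The usual two-proportion formula gives 45%, and simulation of the Pearson test about 46%.
- Score kept, 23% of classical-approach patients at 7 and 50% at 8: p̄ = 0.606 at 8, 0.194 at 7 and 0.20 below. With those below 7 spread evenly, 1 − Σp̄³ = 0.770, z = 2.41, power 67%.

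Simulated power (Pearson on the cut, Mann-Whitney with ties on the score) beside the formula:

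| Assumed classical-approach state | Cut, simulated | Score, simulated | Score, formula |
|---|---|---|---|
| 20 min, 33% at 7, 40% at 8 | 46% | 71% | 71% |
| 20 min, 23% at 7, 50% at 8 | 45% | 65% | 67% |
| 20 min, 8% at 7, 65% at 8 | 47% | 55% | 57% |
| 20 min, 3% at 7, 70% at 8 | 46% | 49% | 52% |
| 25% at 7 or more (assumed 10 min) | 62% | 76% | 78% |
| 5% at 7 or more (assumed 5 min) | 23% | 77% | 78% |

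The last two formula entries assume even spread below 7 and splits of 10%/15% and 3%/2% at 7/8. The simulated losses are 25, 20, 8, 3, 14 and 54 points. At 20 minutes nearly all the gain comes from separating 7 from 8: in the 23% case, lumping all scores below 7 together lowers the formula's power only from 67.3% to 66.8%. At the early times it comes from separating 0 to 6.

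**Without a common odds ratio, 61 per arm.**

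- Four correlated nerves at a single time, 45 scenarios: median loss 11 points, range 1 to 33, and at least 10 points in 60%. At a 73% control rate the loss is 5 to 16.
- Six times with lognormal nerve onset, 18 scenarios: median loss 27 points at 5 minutes, 13 at 10 minutes and about 5 from 15 to 30 minutes. The range at 20 minutes is −1 to 14. Losses above 50 occur only at 5 minutes; the largest at any later time is 40, at 30 minutes. Over all 108 scenario-times, 49% lose at least 10 points.

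**What onset time recovers.** The comparator is a rank test on the score summed over the six times. A rank test on time to 7 or more, with patients who never reach it placed last, loses 1 to 8 points (median 3). In a separate set of simulations it loses 0 to 13 (median about 4). A t test among reachers only loses 0 to 21 (median about 10) in that second set and about 0 to 13 in another. The article does not say which applies, so both are assumptions.

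**The case against.** The strongest reply is that the trial does not rely on the per-time percentages to describe speed. Onset times use all six assessments and measure speed directly, and under a rank test they come close to the full-score analysis. The Abstract also lists onset times of individual nerves, which do not need the combined cut. Complete block is the primary construct, so reporting the same definition over time keeps the secondary results readable beside it. A difference between scores of 3 and 4 at 5 minutes has no stated clinical meaning. The power figures rest on assumed distributions, and the proportional-odds scenarios favour a rank test. A full plan, not shown, might also compare the scores.

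Most of this stands. A reader might infer that the plan discards most of the block-dynamics information, or that a real difference in build-up would probably be missed. The onset-time results do not support either reading. Nor is there a case for demoting the percentages to description only. What remains is narrower: Table 1 fixes the per-time comparison on the cut score, the graded data are already collected, and how much the onset times recover depends on how they are analysed.

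**Conclusion.** The point holds as an optional improvement to the secondary outcomes. Nothing is stated wrongly. Under assumed score distributions, the cut costs roughly 3 to 30 points of power at a given time: about 3 to 25 at 20 minutes under proportional odds, and less in the time-course model, where a few scenarios show no loss. Losses of about 50 or more arise mainly at the 5-minute floor, so a figure of that size should not be quoted as typical. The planned onset times recover much of the loss, more under a rank test with non-reachers last than under a t test among reachers. The binary 20-minute primary outcome, its margin and its sample size are unaffected. The sizes depend on the assumed spread of scores, the effect size borrowed from a pilot of 15 per group, and a two-sided 5% level. The direction is the same in nearly every scenario tried.

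**What to change.** Leave the 20-minute primary outcome, its margin and the percentages at 7 or more as they are. Add to Table 1 and to the statistical analysis section a between-arm comparison of the full sensory score, and one of the full motor score, over 5 to 30 minutes. Each should be one analysis, not six separate tests. Two options would serve:

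- a repeated-measures ordinal model with a patient random effect and a prespecified overall approach effect, reported as an odds ratio with 95% CI; or
- a rank test on the score summed over the six assessments.

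If the model includes an approach-by-time term, state in advance which contrast is the overall effect. State also that the motor score covers the same four nerves, so that its 0 to 8 range is fixed.

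The cost is a little more analysis of data already collected, with no added burden on patients. An odds ratio on the score is less familiar to anesthesiologists than a percentage and assumes roughly proportional odds. The retained percentages cover the first drawback, and the rank test avoids the second.
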